#### Health economics analysis

Cost, cost-effectiveness and cost-utility analyses will be performed using the perspective of the Italian national health service and municipalities. The cost-analysis will be stratified according to allocation group (UP, UP-TECH and control groups) and will include direct costs in terms of: 1) time spent by each social worker, for each patient/caregiver dyad; 2) time spent by other professionals with each patient; 3) time spent training social workers to perform the case management intervention; 4) time and other costs of social workers and nurses for travel; 5) use of drugs for dementia and related costs; 6) use of other drugs and related costs; 7) use of health care and social services; 8) cost of other consumables used for the interventions; and 9) cost of technological devices.

In a separate analysis we will also consider the social costs of AD, defined as the sum of costs incurred providing formal treatment and patient care plus the cost of informal care and the loss of productivity of caregivers. The assistance provided by family caregivers will also be assessed by valuing it equal to the salary of an unskilled care assistant.

The availability of cost data, together with data collection on health care outcomes, such as time to institu-tionalization of the patient and the stress level/quality of life of the caregiver, will allow a cost-effectiveness and cost-utility analysis. We will consider the control group (light care intervention) as the reference group for incremental analysis.

As outcomes measures for economic analysis we will use: 1) change in caregiver burden over a 12-month period; 2) the number of institutionalizations; 3) hospitalizations; and 4) deaths. Since both the costs and the effects of the interventions will occur over a period of 1 year, it will not be necessary to adjust for the time delay and to discount the measures. Four incremental cost-effectiveness ratios (ICERs) will then be calculated by taking the difference in costs divided by the difference in the four outcomes between the groups. The ICERs will represent the additional costs of gaining an additional unit of the above outcome measures through the intervention owing to the case management intervention and the case management plus the technological intervention.

In a following step, probabilistic sensitivity analyses (PSA) will also be performed on the three models using the software, TreeAge Pro 2009 (Williamstown, MA, USA). Results from the PSA will also be presented as an acceptability curve, graphically illustrating the probability of the intervention being cost-effective over a range of willingness to pay values.

A cost-utility analysis will estimate the ratio between the cost of an intervention and the benefit it produces in terms of caregivers' quality-adjusted life years (QALYs). Utility will be measured using the SF-12 administered during the nurse visits [48]. The PSA of this model will follow a similar procedure to that of the cost-effectiveness analysis.

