**Methods/design:**

A total of 450 dyads comprising AD patients and their caregivers in five health districts of the Marche region, Italy, will be randomized into three study arms. Participants in the first study arm will receive comprehensive care and support from a case manager (an *ad hoc* trained social worker) (UP group). Subjects in the second study arm will be similarly supported by a case manager, but in addition will receive a technological toolkit (UP-TECH group). Participants in the control arm will only receive brochures regarding available services. All subjects will be visited at home by a trained nurse who will assess them using a standardized questionnaire at enrollment (M0), 6 months (M6) and 12 months (M12). Follow-up telephone interviews are scheduled at 24 months (M24). The primary outcomes are: 1) caregiver burden, measured using the Caregiver Burden Inventory (CBI); and 2) the actual number of days spent at home during the study period, defined as the number of days free from institutionalizations, hospitalizations and stays in an observation unit of an emergency room.

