Responding to this call and building on the knowledge retrieved in the literature, the Italian National Research Centre on Aging (INRCA) in partnership with the Government of the Marche region, developed the proposal of the UP-TECH intervention study, which was successfully evaluated and funded with a grant of approximately 1 million euros. The ambitious idea underlying this project is to create a multi-component intervention program at regional level, which could engage professionals working in both the social and health care services, in a large-scale organizational change to restructure the processes of AD care. For these reasons, a study has been designed following the trial methodology and adapting to the Marche region the most promising evidence-based interventions in this area.

The main project objectives of the UP-TECH study are: 1) to reduce the care burden of family caregivers of AD patients; and 2) to maintain AD patients at home.

Secondary objectives of the project are: 1) to ensure continuity of care and the integration of care pathways; 2) to create an information management system specific for AD; and 3) to evaluate the cost-effectiveness of a case management program for AD patients and their caregivers.

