## Methods/design

### Study design

UP-TECH is a multi-component, randomized, controlled trial, lasting 12 months, and enrolling dyads composed of an AD patient and their primary family caregiver. A total of 450 dyads, living in five different health districts of the Italian Marche region, will be randomized into three arms: 1) 150 dyads provided with systematic and comprehensive support of a trained social worker acting as case manager and receiving three nurse home visits (UP group); 2) 150 dyads provided with systematic and comprehensive support of a trained social worker acting as case manager, receiving an assistive technology intervention and three nurse home visits (UP-TECH group); and 3) 150 dyads receiving ‘light’ support in the form of a paper brochure and three nurse home visits (control group).

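### The stated economic comparison is with control, so the UP-TECH ratio blends case management with the kit and does not give the kit's own cost-effectiveness

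*Protocol article*

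**What the plan says.** All references are to the protocol article.

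- **Comparator.** Health economics analysis: "We will consider the control group (light care intervention) as the reference group for incremental analysis".
- **Ratios.** The same section says: "Four incremental cost-effectiveness ratios (ICERs) will then be calculated by taking the difference in costs divided by the difference in the four outcomes between the" (the quotation stops one word short of the end). No pair of arms is named in that sentence. The next sentence says the ratios are the extra cost of one more unit of outcome "owing to the case management intervention and the case management plus the technological intervention".
- **Costs.** They are collected separately for UP, UP-TECH and control, and the list of items includes "cost of technological devices".
- **Uncertainty.** The acceptability curve is described as "graphically illustrating the probability of the intervention being cost-effective over a range of willingness to pay values", with the intervention in the singular. The probabilistic sensitivity analysis is to be run on three models that are not defined.
- **Arms.** The Abstract (Methods/design) shows that one active arm contains the other: "Subjects in the second study arm will be similarly supported by a case manager, but in addition will receive a technological toolkit (UP-TECH group".
- **Objective.** The economic objective in the Background is "to evaluate the cost-effectiveness of a case management program for AD patients and their caregivers". The Discussion widens this to the costs and cost-effectiveness of the different interventions.

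**The concern.** Control, UP and UP-TECH are three mutually exclusive strategies of increasing content. A health service that has decided to fund case management must then decide whether to add the kit, and the contrast for that decision is UP-TECH against UP. A ratio of the whole package against control answers a different question.

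If case management is good value and the kit adds little, the package can still look acceptable because case management carries it. If case management is poor value and the kit is cheap and useful, the package ratio hides the kit's merit. In both cases the number printed beside UP-TECH is easily read as a statement about the technology, in a trial whose Discussion says its findings should inform future programmes.

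**Working it through.** The plan states no ratio, cost, effect or willingness to pay, so there is no figure of its own to reproduce. The check is algebra plus assumed figures. Effects are points of reduction in CBI and costs are in euros.

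**Identity.** Let UP add cost a and effect b over control, and let the kit add cost c and effect d over UP. Then

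- UP v control = a/b
- UP-TECH v UP = c/d
- UP-TECH v control = (a + c)/(b + d) = w × (a/b) + (1 − w) × (c/d), with w = b/(b + d).

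With b and d positive, the package ratio is the effect-weighted average of the other two. It equals the kit's own ratio only when those two are equal.

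**Illustrations (all inputs assumed).**

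| Case | a, b | c, d | UP v control | UP-TECH v control | UP-TECH v UP |
|---|---|---|---|---|---|
| 1 | 1,000, 4 | 800, 1 | 1,000/4 = 250 | 1,800/5 = 360 | 800/1 = 800 |
| 2 | 3,000, 4 | 200, 2 | 3,000/4 = 750 | 3,200/6 = 533 | 200/2 = 100 |

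Check of the identity: case 1, 0.8 × 250 + 0.2 × 800 = 360; case 2, (4/6) × 750 + (2/6) × 100 = 533.

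**Case 1: the kit looks better than it is.** At an assumed 500 per point, UP-TECH passes against control (360) while its increment over UP fails (800). Net monetary benefit against control is 500 × 4 − 1,000 = 1,000 for UP and 500 × 5 − 1,800 = 700 for UP-TECH, so UP is preferred.

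**Case 2: the kit looks worse than it is.** The package costs 533 per point, but the kit itself costs 100. Here UP is extendedly dominated (533 is below 750), so in a choice among all three strategies UP-TECH is rightly compared with control. The 100 is what matters to a district that already provides case management. This is why UP-TECH v UP should be reported even when the ranking removes UP.

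**Range over the kit's effect.** Take UP at 1,000 for 4 points, the kit at +500, and 400 per point as the threshold:

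| Kit's added gain | UP-TECH v control | UP-TECH v UP |
|---|---|---|
| 0 | 1,500/4 = 375 | dominated by UP |
| 0.25 | 1,500/4.25 = 353 | 2,000 |
| 0.5 | 1,500/4.5 = 333 | 1,000 |
| 1 | 1,500/5 = 300 | 500 |
| 2 | 1,500/6 = 250 | 250 |

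UP-TECH passes against control in every row. The kit's own increment fails for any gain from 0 to just below 500/400 = 1.25 points.

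**What the ratios alone leave open.** The pair 250 and 375 arises from UP 1,000/4 and UP-TECH 1,500/4, where UP dominates UP-TECH. It arises equally from UP 1,000/4 and UP-TECH 1,875/5 = 375, where the kit buys 1 point for 875. The two published ratios cannot tell these apart.

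**The case against.** **The text does not exclude UP-TECH v UP.** It names a reference group, costs each arm in its own right, takes differences between groups and mentions three models. The count is loose too: four ratios means one per outcome, whereas two interventions on four outcomes make eight. This stands as far as it goes. A reader might infer that comparisons are made only against control; that is an inference from the named reference and the absence of any other contrast, not something the protocol says. But the vague phrases do not supply the missing contrast, and the sentence on what the ratios represent lists the two interventions and not the kit.

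**The package question is the one asked.** The stated objective names case management, and the second ratio is openly labelled as case management plus technology. This stands, and it limits the weight of the point. It does not remove it, because the section itself extends the ratios to the technology arm and the Discussion promises cost-effectiveness of the different interventions.

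**The components give the answer by subtraction.** If cost and effect differences are published with the ratios, the point estimate for UP-TECH v UP follows. Its uncertainty does not follow from the two separate control contrasts and needs its own analysis.

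**A condensed article leaves detail to the full plan.** That is fair for ranking rules and net-benefit methods, whose absence is no fault here. The reference group, however, is a choice that the article states.

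**Stronger readings that fail.** A reader might infer that the plan always flatters the technology; case 2 shows the reverse. A reader might infer that extended dominance cannot be detected; when effects rise from control to UP to UP-TECH, UP is extendedly dominated exactly when the UP-TECH ratio against control is the lower of the two. A reader might add that ratios per death avoided can have denominators near zero; the documents give no death rate, and that difficulty is no smaller for UP-TECH v UP, so it does not bear on the choice of comparator.

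**Conclusion.** The point holds in a limited form. The plan names control as the reference for incremental analysis, describes ratios for UP and for the UP-TECH package, and states no UP-TECH v UP contrast. Because UP-TECH is UP plus the kit, its ratio against control does not measure the kit's value and can differ from it in either direction: 360 against 800, or 533 against 100, in the illustrations.

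The identity needs only positive effect increments. The sizes rest entirely on assumed costs, effects and thresholds, and the plan fixes no decision rule. The point concerns a secondary objective and leaves the two primary outcomes untouched. It should be corrected before the economic analysis is done.

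**What to change.** Replace the common-control reference with a full incremental analysis. Suggested text:

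> The three strategies will be ordered by mean cost. Dominated and extendedly dominated strategies will be removed, and each remaining strategy will be compared with the next less costly one. UP-TECH versus UP will always be reported, with its uncertainty. Net monetary benefit and cost-effectiveness acceptability curves will be presented for the three strategies jointly. Ratios against control will be supplementary.

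Report the cost and effect differences beside every ratio, define the three models used in the probabilistic sensitivity analysis, and say how many ratios will be calculated for which pairs of arms.

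The cost is a few lines in the economic plan and a little more analysis. Costs by arm and device costs are already to be collected. The drawback is that UP-TECH v UP will be less precise, and its ratio unstable, if the kit adds little; net benefit is the better summary in that case.

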### Nurse home visits and light support

All dyads participating in the UP-TECH group will receive three home visits by a specifically trained nurse. Home visits will occur at enrollment (M0), 6 months (M6) and 12 months (M12). Each visit will occur with the following steps: 1) telephone contact between the nurse and the family caregiver; 2) collection of informed consent (only at M0) and administration of the UP-TECH questionnaire; and 3) brief counseling/training of the caregiver regarding practical aspects of patient assistance, such as daily management of drug treatment, ergonomics of the home environment, stress management and care burden.

The creation of an information package for the 150 family caregivers included in the control group, illustrating the range of social and health services available in the local community, is planned. The information package will be delivered to the caregiver during home visits by the nurse. These caregivers and their families will continue to receive services in accordance with the usual care procedure, which, as already mentioned, does not include any other specific service from the health and social care systems. Some patients might receive additional care services, but this does not occur within the framework of an integrated case management program, and will depend on the presence of other pathological and social conditions.

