The family caregiver will be given a questionnaire consisting of five sections: section D, demographic and socio-economic status: age, sex, housing, income and social network support using the Multidimensional Scale of Perceived Social Support (MSPSS) [45]; section E, lifestyle: information regarding diet, smoking and alcohol consumption; section F, clinical evaluation: information on the perception of caregiver depression and anxiety (HADS) [40], the perception of well-being of the caregiver (quality of life questionnaire, SF-12) [38], and the presence of chronic diseases; section G. anthropometric measurements, including control of blood pressure and measurement of body mass index (BMI), via evaluation of height and weight; and section H, the caregiving relationship: caregiver burden measured with the CBI [36] and the risk of domestic abuse in the caregiving relationship [42].

In the last section of the questionnaire (section I, consumption of resources by the AD patient), the family caregiver will be asked for information regarding: resource consumption of the AD patient (for example drug therapy, visits to general practitioners and specialists, use of home nursing, and hospitalizations); use of treatment/care (for example nurse and formal caregiver) paid for by the patient/caregiver dyad, expressed in number of hours per week of treatment (or care); and the number of hours of work lost by the caregiver (hours per week) to provide assistance for the AD patient (productivity loss).

After the start of the study, at 6 months (M6) and 12 months (M12), respectively, a second and a third assessment will be conducted. Twelve months after the end of the trial (M24), follow-up telephone calls will be made to study participants in order to assess the impact of the interventions over the medium term.

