#### Statistics

The first step of the analysis will be exploratory in nature. A descriptive analysis of the sample will be conducted using uni- and bi-variate statistical analyses, with the aim of verifying the comparability of the three study groups. Significant differences between exposures and outcomes will be compared using the chi-square test, Fisher’s exact test (in the case of categorical variables), t-test or analysis of variance (ANOVA) test (for comparisons of continuous variables between groups according to a normal or non-normal distribution). Additionally, to check possible selection bias, the characteristics of the subjects in the sample will be compared to those of non-respondents for available variables (for example age, gender, place of living and MMSE score).

The primary outcome, caregiver burden inventory, will be compared between the three groups using analysis of covariance (ANCOVA). The analyses will adjust for variables which are non-homogenously distributed in the three groups and control for other factors that the literature suggests are associated with the two outcomes (for example gender and age of caregivers, severity of dementia, and use of private care workers) [46,47].

The primary outcome, number of days spent at home by the AD patient during the observation period, will be similarly analyzed using ANCOVA. The events of hospitalizations and institutionalization will also be analyzed with the following: the distribution of events and event-free survival (days spent at home) will be described for the entire sample using Kaplan-Meier estimator modeling; Mantel-Cox log-rank test or generalized Gehan-Breslow-Wilcoxon test will be used to evaluate bivariate differences in survival distribution between identified subgroups; Cox proportional hazard modeling will be used to analyze the multivariate effects of identified risk factors and other determinants on time spent at home under the proportional hazards assumption; and adjusted hazards ratio (HR) and 95% confidence intervals (CI) will be calculated to test the direction and strength of the influence of individual factors on event-risk and event-free survival. The analyses of outcomes will be intention-to-treat (ITT).

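### The burden ICER is built on 12-month change in CBI with no stated adjustment for M0 CBI, which costs precision that the trial's own baseline data would recover

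*Protocol article*

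**What the plan says.** Health economics analysis lists four effect measures. The first is "change in caregiver burden over a 12-month period"; the others are institutionalizations, hospitalizations and deaths. The ICERs "will then be calculated by taking the difference in costs divided by the difference in the four outcomes between the groups". Uncertainty is handled by probabilistic sensitivity analysis (PSA) and an acceptability curve. For the cost-utility analysis the same section says "Utility will be measured using the SF-12 administered during the nurse visits". It gives no QALY formula and no rule for baseline utility.

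Under Statistics, the clinical CBI comparison is specified differently: burden "will be compared between the three groups using analysis of covariance (ANCOVA"), with adjustment for variables that turn out unevenly distributed and for factors suggested by the literature. M0 CBI is not among the examples of covariates given there.

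The baseline data exist. The Abstract has all subjects assessed at M0, M6 and M12, Study design gives three nurse visits to each of the three arms, and Assessments puts both the CBI (section H) and the SF-12 (section F) in the caregiver questionnaire.

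**The concern.** For burden, the article names both the effect measure and the form of the estimator: a between-group difference in change. Subtracting M0 CBI in full assumes that a one-point baseline difference carries forward as one point at M12. When the M12-on-M0 slope is below 1, it carries forward as less. An arm that starts high by chance then falls further through regression to the mean, and the change score counts that fall as effect. Randomization, allocation and blinding describes blocks of 15 and no stratification on CBI, so chance imbalance in M0 CBI is not constrained by design.

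The CBI difference is the denominator of the burden ICER, so avoidable noise in it goes directly into the ratio. Cost-effectiveness of case management is a stated secondary objective, and the Discussion expects definitive evidence on it to inform welfare reform. The clinical section names ANCOVA for the same scale, and nothing says whether that estimate is the one used in the ICER.

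**Working it through.** **Plan's own figure.** The article gives no figure for the economic analysis. The nearest is the CBI sample size under Sample size calculation. Two-sided, (18² + 12²) × (1.960 + 0.842)² / 8.5² gives 51 per arm, or 60 after 15% drop-out, so 150 is more than 80% power requires (power is 99.3% at 127.5 per arm). The point here does not depend on that figure.

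**Inputs.**
- SD 18 at M0 and in control; SD 12 in treated at M12; planned difference 32.5 − 24 = 8.5 (Sample size calculation).
- 150 × 0.85 = 127.5 evaluable per arm.
- M0-M12 correlation r: not in the document. Assumed 0.5, with the range 0.3 to 0.8 shown.
- Treated SD at M12: either the plan's 12, or 18 in both arms as a more cautious alternative.

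**Equal SDs (18 and 18).**
- Change score: SE = 18 × √(2(1 − r)) × √(2/127.5). At r = 0.5 this is 2.25.
- Adjusted for M0: SE = 18 × √(1 − r²) × √(2/127.5). At r = 0.5 this is 1.95.
- The ratio is √((1 + r)/2), so the SE falls by 13% at r = 0.5.

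**Plan SDs (18 and 12).**
- Change score, variances summed over the two arms: (324 + 324 − 648r) + (324 + 144 − 432r) = 1116 − 1080r. At r = 0.5 this is 576, and SE = √(576/127.5) = 2.13.
- Adjusted with a common slope b = (r × 18/18 + r × 12/18)/2 = 0.833r, or 0.417 at r = 0.5. The residual variances are 245.25 and 110.25, sum 355.5, and SE = √(355.5/127.5) = 1.67. In general the sum is 468 − 450r².
- M12 CBI alone, ignoring baseline: √(468/127.5) = 1.92. On these SDs the change score is less precise than not using baseline at all until 1116 − 1080r < 468, that is r > 0.6.
- A simulation of 4,000 trials with 127 per arm at r = 0.5 gave empirical SEs of 2.15 and 1.65, with both estimators centred on −8.5.

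**Effect of a chance imbalance.** The SE of the M0 difference is 18 × √(2/127.5) = 2.25 points. A one-SE imbalance moves the change-score effect away from the adjusted effect by (1 − slope) × 2.25.

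| r | SE change → adjusted, SD 18/18 | SE cut | Shift | SE change → adjusted, SD 18/12 | SE cut | Shift |
|---|---|---|---|---|---|---|
| 0.3 | 2.67 → 2.15 | 19% | 1.58 | 2.49 → 1.83 | 27% | 1.69 |
| 0.5 | 2.25 → 1.95 | 13% | 1.13 | 2.13 → 1.67 | 21% | 1.3 |
| 0.7 | 1.75 → 1.61 | 8% | 0.68 | 1.68 → 1.39 | 17% | 0.94 |
| 0.8 | 1.43 → 1.35 | 5% | 0.45 | 1.41 → 1.19 | 15% | 0.75 |

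At r = 0.5 the shift is 1.13/8.5 = 13% to 1.3/8.5 = 15% of the planned effect.

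**The case against.** The strongest reply is that the quoted formula is simply the definition of an ICER. A regression-adjusted difference is also a difference between groups, and change as an outcome does not exclude adjustment: regressing change on arm and M0 CBI gives the same arm effect as regressing M12 CBI on arm and M0 CBI. This is correct. It means the fix is compatible with the chosen outcome and costs nothing. It does not supply the missing covariate, and a reader following the sentence literally would compute the unadjusted contrast.

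Several stronger readings are tempting, and the article does not support them:
- **That it prescribes raw or unadjusted differences.** It uses neither word. It states a difference in change and mentions no adjustment.
- **That it ignores baseline burden.** The change score uses M0 CBI; the fault is over-correction.
- **That QALYs will be left unadjusted.** The cost-utility text does not say how QALY differences are estimated, and an article may leave that to the full plan. A size for this effect would need QALY weights, correlations and a utility SD that are not given.
- **That all four ICERs suffer.** Institutionalizations, hospitalizations and deaths contain no M0 CBI term.
- **That the result is biased.** Under randomisation the imbalance is zero on average. The cost is imprecision, and error conditional on the imbalance that occurs.
- **That the trial will report two conflicting CBI effects.** The Statistics section names ANCOVA but not M0 CBI as a covariate, so this is possible but not established.

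It is also fair to say that the larger gain relies on the hypothetical treated SD of 12, and that the effect on the PSA cannot be quantified because cost variances and input distributions are not given.

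**Conclusion.** The point holds for the burden ICER and is of modest weight. The effect measure stated there, used without M0 CBI as a covariate, is valid but less precise than the collected data allow. It also carries part of any chance M0 imbalance into the denominator. At r = 0.5 the SE is 13% lower after adjustment with equal SDs and 21% lower with the plan's SDs. With equal SDs the gain runs from 5% (r = 0.8) to 19% (r = 0.3). The result rests on the assumed correlation, the 15% drop-out and the SDs from the sample-size section. The QALY remark is a request for clarification only.

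**What to change.** In Health economics analysis, state that the incremental CBI effect comes from a regression of M12 CBI (or, equivalently, of 12-month change) on arm, with M0 CBI named as a covariate. Use the same model for the clinical CBI comparison under Statistics and name M0 CBI there too. Carry the adjusted difference and its SE into the burden ICER, the PSA and the acceptability curve. As a minor clarification, add that QALY differences are adjusted for M0 SF-12 utility.

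This is a few sentences of wording, with no new data, visits or participants. The only downside is that the economic CBI effect is no longer a simple difference of table means.
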